### Diabetes classification

Prevalent diabetes was determined according to physician reports to the chronic disease registry of Clalit Health Services. Incident diabetes will be determined by any one of the following criteria: two fasting glucose readings of 126 mg/dl or above during the course of a year, HbA1c greater than 7.0%, 3 recorded purchases of glucose-lowering medications during the course of a year, diagnosis of diabetes according to the Chronic Disease Registry of Clalit Health Services, or a written diagnosis by a physician (in the community or hospital). The relatively low number of individuals classified with diabetes at study entry (prevalent diabetes) is apparently due to the more limited definition of diabetes used by Clalit Health Services prior to 2002.

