### Exposure to glucose-lowering medications

In addition to the exposure to diabetes per se, individuals with diabetes will be studied for their exposure to glucose-lowering medications. A drug exposure will be defined as a minimum of 3 purchases of glucose-lowering medications during one year. Each drug exposure will define one type of treatment or a combination of treatments. An individual may be analyzed according to more than one exposure during follow-up time. Drug exposures to be investigated are: each insulin type, meglitinide derivatives, sulfonylureas, biguanides, alpha glucosidase inhibitors, thiazolidinediones, and incretins. An additional group (“no glucose-lowering medication”) will comprise periods of time during which individuals classified with diabetes did not yet purchase glucose-lowering medications.

For each glucose-lowering medication, cumulative exposure will be assessed as the total number of monthly dosages purchased. Daily dosages and daily dosages per body weight will be estimated from records of purchases. Time dependent regression models for the outcomes investigated will account for glucose-lowering medications as they are added and changed over the follow up period, adjusting for constant and time-dependent covariates.

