### Potential confounders

The following variables will be included together with the time they were recorded:

1. Age, gender, BMI, type of medical insurance (basic, or basic and supplementary).

2. Smoking status (non-smoker, former smoker, current smoker)

3. Concomitant medications (types, exposure rates, and cumulative exposures), including antihypertensive, lipid lowering, beta-blockers, angiotensin converting enzyme (ACE) inhibitors

4. Comorbidities defined according to the Clalit Registry of Chronic Diseases, with focus on those associated with cancer risk (e.g. IBD, COPD, gallstones)

5. Blood pressure (mean annual values)

6. Reproductive factors: hormone replacement therapy, fertility treatments

7. Biochemical characteristics (first and last tests during follow-up, mean annual values, and number of blood tests performed annually): serum lipids (total cholesterol, triglycerides, HDL-cholesterol, VLDL-cholesterol), liver enzymes, creatinine, and urine protein

8. Clinical examinations (average annual number of visits to the treating physician during follow-up)

9. Cancer screening tests: mammography, fecal occult blood, colonoscopy, PAP smear, colposcopy, prostate screening (PSA, ultrasound)

10. Medical procedures associated with cancer risk (e.g. cholecystectomy).

We note that data on some key potential confounders (like smoking and fertility treatments) are available for only a subset of the cohort. We will conduct sensitivity analyses in these subsets to assess whether these factors indeed confound the associations between diabetes, glucose-lowering medications, and cancer.

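### Three drug purchases in a year are enough to define incident diabetes and also define drug exposure, with no exclusion for pregnancy or non-diabetic use, so purchase-only false positives can enter the treated groups but not the untreated one

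*Protocol article*

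**What the plan says.** The Diabetes classification section of the protocol article sets a rule for new cases: "Incident diabetes will be determined by any one of the following criteria". The five criteria are "two fasting glucose readings of 126 mg/dl or above during the course of a year", an HbA1c above 7.0%, "3 recorded purchases of glucose-lowering medications during the course of a year", a registry entry, and a physician's written diagnosis. Each is sufficient alone. The purchase criterion asks for no indication, laboratory value or diagnosis.

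The section on exposure to glucose-lowering medications sets the same threshold: "A drug exposure will be defined as a minimum of 3 purchases of glucose-lowering medications during one year". The drugs counted are "each insulin type, meglitinide derivatives, sulfonylureas, biguanides, alpha glucosidase inhibitors, thiazolidinediones, and incretins", so insulin and metformin (a biguanide) are included. The untreated comparison group is the time during which people already classed as diabetic had not yet bought any such drug.

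Eligibility is age 21 or older plus continuous insurance. The only reproductive entry under Potential confounders is "Reproductive factors: hormone replacement therapy, fertility treatments". Pregnancy is not listed, and fertility data are said to exist for only part of the cohort.

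**The concern.** Under the rule as written, a woman without lasting diabetes who buys insulin three times during one pregnancy, or metformin three times as part of fertility treatment, becomes an incident diabetic. The same purchases make her a drug-exposed diabetic in Aim 3. The article describes no way for a person to leave the diabetic class.

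Three aims are touched:
- **Aim 1 (diabetes against no diabetes):** false positives dilute the incident-diabetes association.
- **Aim 2 (glucose control):** people without diabetes would tend to sit at the low end of the glucose range and could alter the gradient.
- **Aim 3 (medications):** false positives from the purchase criterion fall on one side of the treated-untreated comparison.

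Prevalent diabetes rests on the registry alone. The prevalent and incident strata, which the analysis keeps separate, may therefore differ in how specific the diagnosis is.

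**Working it through.** **Inputs from the article.** Cohort over 2,300,000; prevalent diabetes over 110,000; incident diabetes 350,000. No misclassification rate is given, so there is no stated figure to reproduce on this point. Incident cases among those free of diabetes at entry are 350,000 / (2,300,000 - 110,000) = 16.0%. This figure is not evidence of false positives, because the article attributes the low prevalent count to a narrower definition before 2002.

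**Step 1: where false positives can fall.**
- Purchases only: the person has already bought the drug when classified, so contributes no untreated diabetic time. These cases fall in treated groups only.
- Laboratory only (for example two raised fasting values in one illness or steroid course): the person need not have bought any drug. These cases can fall in untreated time, or in treated time if purchases follow.

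**Step 2: dilution in Aim 1.** Let f be the share of incident cases who do not have diabetes, and assume they carry the non-diabetic cancer rate. Then observed HR = 1 + (1 - f)(true HR - 1).

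| Assumed f | Persons (f x 350,000) | True HR 1.20 appears as | True HR 1.40 appears as |
|---|---|---|---|
| 1% | 3,500 | 1.198 | 1.396 |
| 5% | 17,500 | 1.19 | 1.38 |
| 10% | 35,000 | 1.18 | 1.36 |
| 20% | 70,000 | 1.16 | 1.32 |

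**Step 3: younger women.** Every input here is an assumption: 300,000 to 600,000 women aged 21-45, of whom 1.5% to 5% meet the purchase criterion over ten years for pregnancy or a fertility indication.
- Low: 300,000 x 1.5% = 4,500. High: 600,000 x 5% = 30,000. Divided by 350,000, these are 1.3% and 8.6% of all incident cases. A true HR of 1.30 would then appear cohort-wide as 1 + 0.987 x 0.30 = 1.296 and 1 + 0.914 x 0.30 = 1.274.
- Within the stratum, the population size cancels: share = a / (a + t), where a is the purchase-only percentage and t the true ten-year diabetes incidence.
- With t = 5%: 1.5/6.5 = 23% and 5/10 = 50%, so HR 1.30 appears as 1.23 and 1.15.
- With t = 16% (the cohort-wide figure, presumably too high for young women): 1.5/17.5 = 8.6% and 5/21 = 23.8%, so HR 1.30 appears as 1.27 and 1.23.

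**Step 4: direction in Aim 3.** Suppose the drug has no effect and diabetes carries HR 1.20. With 5% false positives in the treated group only, treated against untreated is 1.19/1.20 = 0.992. With 5% in the untreated group only, it is 1.20/1.19 = 1.008. With equal shares it is 1.00. The sign depends on which side holds the larger share, and the article does not say. It also depends on false positives carrying the average non-diabetic rate. That may fail for fertility indications and female cancers.

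**The case against.** The strongest reply is that this is a condensed article, and that code lists and the handling of gestational diabetes may be in a fuller document. That may be so. However, the article gives a complete operational rule with thresholds, counts and time windows, and an unshown exclusion would change it. If one exists, the definition needs only a sentence to say so.

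The article also has partial safeguards:
- The fasting glucose criterion needs two readings in a year, although both may fall in one pregnancy or illness.
- Sensitivity analyses are promised in the subset with fertility data.
- Cancer-prevalent people are analysed separately, with their own adjustments and propensity scores.
- Aim 3 takes HbA1c and fasting glucose into account and models cumulative dose, so brief use adds little dose.

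These reduce the problem, but none varies the diabetes definition. The prior event rate ratio method applies only to incident diabetes, so it inherits the same classification.

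A reader might infer that the treated groups are contaminated while the untreated comparator is clean, so that metformin would look protective. The article does not support this, because laboratory false positives can enter untreated time. Nor are off-indication buyers wrongly counted as drug users: they did buy the drug, and only their diabetes label is in doubt.

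**Conclusion.** The definition permits misclassification that the planned analyses do not examine, and its purchase-only part can reach only the treated groups. That follows from the text without any outside figure.

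The size does not follow from the text. Cohort-wide dilution is probably small: at an assumed 5% misclassified, HR 1.20 becomes about 1.19. This rests on false positives carrying the non-diabetic cancer rate. The effect is likely larger for site-specific results in younger women. A reader might take the 23% to 50% range as an estimate for them, but it comes from assumed inputs with true incidence set at 5%, and it falls to about 9% to 24% if that incidence is 16%. The net direction in Aim 3 is not established. The documents show that people without diabetes can be classed as incident diabetics; they do not show how many would be.

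The point merits a change to the definition and one added sensitivity analysis. It does not show that the study's main results would be wrong.

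**What to change.** 1. In Diabetes classification, do not count glucose values or drug purchases that fall within a recorded pregnancy and a short, stated period after delivery.
2. Flag people who qualify by purchases alone, and repeat Aims 1-3 without them as a pre-specified sensitivity analysis.
3. In that analysis, define confirmation as a laboratory criterion, registry entry or physician diagnosis recorded on or before the classification date. Alternatively, move the classification date to the date of confirmation. Accepting confirmation at any later time would use future information in a time-dependent model and favour people who survive long enough to be confirmed.

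**Cost:** revised definition wording and a query on dispensing, laboratory and diagnosis data that Data management says are in the warehouse. Pregnancy is not a listed variable, so this assumes that pregnancies and deliveries can be identified from recorded diagnoses.

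**Downside:** some well-controlled people with true diabetes but no recorded confirmation drop out of the sensitivity analysis, or are classified later in it.

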### Exposure to glucose-lowering medications

In addition to the exposure to diabetes per se, individuals with diabetes will be studied for their exposure to glucose-lowering medications. A drug exposure will be defined as a minimum of 3 purchases of glucose-lowering medications during one year. Each drug exposure will define one type of treatment or a combination of treatments. An individual may be analyzed according to more than one exposure during follow-up time. Drug exposures to be investigated are: each insulin type, meglitinide derivatives, sulfonylureas, biguanides, alpha glucosidase inhibitors, thiazolidinediones, and incretins. An additional group (“no glucose-lowering medication”) will comprise periods of time during which individuals classified with diabetes did not yet purchase glucose-lowering medications.

For each glucose-lowering medication, cumulative exposure will be assessed as the total number of monthly dosages purchased. Daily dosages and daily dosages per body weight will be estimated from records of purchases. Time dependent regression models for the outcomes investigated will account for glucose-lowering medications as they are added and changed over the follow up period, adjusting for constant and time-dependent covariates.

### Potential confounders

The following variables will be included together with the time they were recorded:

1. Age, gender, BMI, type of medical insurance (basic, or basic and supplementary).

2. Smoking status (non-smoker, former smoker, current smoker)

3. Concomitant medications (types, exposure rates, and cumulative exposures), including antihypertensive, lipid lowering, beta-blockers, angiotensin converting enzyme (ACE) inhibitors

4. Comorbidities defined according to the Clalit Registry of Chronic Diseases, with focus on those associated with cancer risk (e.g. IBD, COPD, gallstones)

5. Blood pressure (mean annual values)

6. Reproductive factors: hormone replacement therapy, fertility treatments

7. Biochemical characteristics (first and last tests during follow-up, mean annual values, and number of blood tests performed annually): serum lipids (total cholesterol, triglycerides, HDL-cholesterol, VLDL-cholesterol), liver enzymes, creatinine, and urine protein

8. Clinical examinations (average annual number of visits to the treating physician during follow-up)

9. Cancer screening tests: mammography, fecal occult blood, colonoscopy, PAP smear, colposcopy, prostate screening (PSA, ultrasound)

10. Medical procedures associated with cancer risk (e.g. cholecystectomy).

We note that data on some key potential confounders (like smoking and fertility treatments) are available for only a subset of the cohort. We will conduct sensitivity analyses in these subsets to assess whether these factors indeed confound the associations between diabetes, glucose-lowering medications, and cancer.

### Outcomes

Incidence of cancer (both first and second primary neoplasms) will be the primary outcome. For diagnoses of cancer, the following data from the Israel National Cancer Registry will be linked to the study file: date of diagnosis; place of diagnosis; hospital or other reporting source; disease type, site, morphology, and stage at diagnosis; tumor behavior (in-situ, benign, malignant, borderline, and uncertain); basis of diagnosis (pathology report, clinical only, imaging devices, or based on death certificates only); and mortality data. Mortality data is continuously updated by reports from the Ministry for Internal Affairs.

### Data management

A database will be constructed for the proposed study from the Clalit Health Services data warehouse. Available are demographic data and vital status from the Israeli Ministry of Interior Affairs and the National Insurance Institute (Social Security); drug dispensing data from pharmacies; and medical data such as laboratory tests, imaging results, diagnoses and clinical data (blood pressure, weight, height, etc.) from Clalit Health Services in-house facilities, as well as from outside suppliers. The data are accessible at the member level, and linked to all registries, including the Cancer Registry, by means of a national identification number, a unique identifier possessed by all Israeli citizens. Data will be organized according to the BI (business intelligence) schema or infrastructure and are extracted using BI programs. Extraction is executed via the BO (business object) and SQL server management studio programs, depending on the complexity and diversity of the data requested from the data warehouse. BI analyst specialists will conduct the extraction and merge the data.

### Power calculation

The most conservative estimates yield at least 175,000 incident cases of cancer in the total cohort. Thus, adequate power is expected for a large number of cancer types and treatment regimens. The sample size for analysis will decrease as the number of treatment switches increases and as certain combinations become rare. Nevertheless, power will be adequate to find relatively small differences based even on subsets of 500–1000 events for a particular treatment or treatment combination. Specifically, we will have over 80% power (based on two-tailed testing at the 0.05 level) to detect a hazard ratio of 1.4 for two subsets of 6000 persons each.

### Statistical analyses

For our first specific aim, we will compare, after adjustment, all and site-specific cancer rates between individuals with and without diabetes. For the second aim, we will investigate whether metabolic control, as indicated by HbA1c and blood glucose levels, is related to cancer risk. Third, we will evaluate differences in outcomes that associate with the use of one or a combination of glucose-lowering treatments. In all of these analyses we will stratify persons with diabetes by those who were already diagnosed with diabetes at study entry (prevalent diabetes), and those who were diagnosed during follow-up (incident diabetes).

Preliminary data analysis will employ standard methods, starting with calculation of person years and age-gender standardized cancer incidence rates for all sites and selected sites in non-diabetics, and in prevalent and incident diabetics without prevalent cancer. These methods will also be used to investigate potential confounding variables such as baseline smoking status and body mass index. In our analyses of Specific Aims 2 and 3, we will then proceed to use Cox regression with time-dependent treatment variables. For Specific Aim 2, the model will include current and past levels of Hba1c and blood glucose, investigating the level above selected thresholds cumulated over the past n years, where n may be between 1 and 5. For Specific Aim 3 the model will include current and previous treatments. For example, we will investigate exposure to a specific medication when expressed by the cumulative dose or by the cumulative dose over the past 1–5 years. We will investigate exposure to multiple medications, first by models that postulate independent multiplicative effects on cancer incidence rates (no interaction model); and if there are sufficient data, we will proceed to examine interactions between medications on cancer incidence. Due to data limitations, it is unlikely that anything more than pairwise interactions will be able to be examined satisfactorily. The analyses of glucose-lowering medications will take into account the clinical factors (HbA1c, fasting glucose) that may have triggered the change. We will, for example, use the methods of Walker, White, and Babiker
[21] to better evaluate how HbA1c triggers treatment changes. This may or may not be important for cancer incidence analyses, depending on whether HbA1c and fasting plasma glucose are or are not related to cancer incidence (see Specific Aim 2). In analyses of Specific Aims 2 and 3, we will also be cautious of the possibility of reverse causation, whereby early physiological changes before the diagnosis of cancer may cause deterioration in glucose control and subsequent change in diabetes treatment. We will therefore investigate whether early peaks in cancer incidence rates follow a change in treatment, and will examine model results when all cancer diagnoses are moved backwards in time by a set period of 2 years, 1 year, or 6 months.

As outlined above, in specific analyses, multiple independent sensitivity analyses will be used more generally to test our model assumptions and the robustness of our results. We will look at varying time intervals for the piecewise exponential models, stratification for departures from proportional hazards, interactions and time-dependent models including lagged predictors. Propensity scores will be used as an alternative to direct confounder adjustment, to control for confounding by indication, and to check the robustness of conclusions. We will also explore results obtained by applying the recently described “prior event rate ratio” method of Tannen, Weiner, and Xie
[22], to the analysis of glucose-lowering medications. Though this method will only be applicable to incident cases of diabetes, its effectiveness in controlling for confounding by indication has been reported.

Cancer prevalent cases will be analyzed separately and will have separate adjustments performed, including separate propensity scoring. This is to overcome potential confounding factors associated with cancer treatments and their residual effects. Furthermore, the risk of second primary neoplasms has not been analyzed in diabetes patients, and might have a different pattern of associations with the disease itself and with the use of glucose-lowering therapies than does the risk of first primaries.

The primary analysis will be performed using PROC PHREG of SAS version 9.2, which allows both Cox-proportional hazards models with time-dependent variables and piecewise exponential models. The piecewise exponential model divides time-at-risk into a set of pre-specified intervals with constant baseline hazard in each interval; the use of multiple intervals allows the hazard to vary with time. Clinically important time dependent covariates for the regression models include age, cholesterol (total, LDL, and HDL), concomitant medications (such as statins, beta-blockers, angiotensin converting enzyme inhibitors, and hormone replacement therapy), smoking, body mass index, blood pressure, co-morbidities (such as cardiovascular disease), and reproductive history. For each continuous variable, we will investigate appropriate transformations and interactions that might improve goodness-of-fit. The proportional hazard assumption will be evaluated using log-log survival plots, examination of Schoenfeld residuals, and testing of interactions between variables and time.

While we can not describe, or even anticipate, every contingency for this comprehensive project, we are confident that the very well qualified team has the expertise to evaluate the data.

This study was approved by the ethics committees of Sheba Medical Center, Tel Hashomer and Clalit Health Services, Israel.

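### The Aim 2 and Aim 3 models use glucose and drug exposure up to the risk date with no lag, and none of the planned lagged analyses is designated primary

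*Protocol article*

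**What the plan says.** All of the following is in the Protocol article, Statistical analyses.

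- **Aim 2 exposure.** "For Specific Aim 2, the model will include current and past levels of Hba1c and blood glucose", with the further option of "investigating the level above selected thresholds cumulated over the past n years, where n may be between 1 and 5".
- **Aim 3 exposure.** "For Specific Aim 3 the model will include current and previous treatments". Exposure to a given drug is examined "when expressed by the cumulative dose or by the cumulative dose over the past 1–5 years".
- **The threat.** For these two aims the authors say they will be cautious of reverse causation, in which "early physiological changes before the diagnosis of cancer may cause deterioration in glucose control and subsequent change in diabetes treatment".
- **The response.** They will look for early peaks in cancer incidence after a treatment change, and will examine the models with all diagnoses moved back by 2 years, 1 year or 6 months. The next paragraph, on sensitivity analyses, lists "stratification for departures from proportional hazards, interactions and time-dependent models including lagged predictors".
- **A partial safeguard for Aim 3.** The drug analyses are to allow for the HbA1c and fasting glucose values that may have prompted a change. Separately, the section on exposure to glucose-lowering medications counts a drug as an exposure only after at least 3 purchases in one year.
- **Primary analysis.** This is tied to a software procedure and a model class (Cox or piecewise exponential with time-dependent variables). No lag is mentioned.

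**The concern.** A current level, a current treatment, a total cumulative dose and a dose over the last few years all count records up to the day at risk. If an undiagnosed cancer raises glucose, and the raised glucose leads to a new or intensified drug, those records are partly a consequence of the outcome. A drug with no effect on cancer, or a high current HbA1c, could then show a raised hazard ratio.

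The plan recognises this route for exactly these aims, yet it keeps the unlagged exposure in the model definitions and leaves the lag to checks. With at least 175,000 incident cancers expected in the cohort, random error will be small for common exposures. A modest bias could therefore look like a precise effect, and more data would not remove it. With three lag lengths, windows of 1 to 5 years and no designated primary, the choice of result to emphasise could also be made after the results are seen.

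**Working it through.** **1. The plan's own power figure.** The Power calculation section claims over 80% power, two-sided 0.05, for a hazard ratio of 1.4 with two subsets of 6000. For equal groups the Schoenfeld formula gives

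d = 4 × (1.960 + 0.842)² / (ln 1.4)² = 278 events,

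which is 278 / 12,000 = 2.3% of the two subsets. No event rate is given for the subsets, so the figure cannot be reproduced exactly. At the cohort average of 175,000 / 2,300,000 = 7.6%, 12,000 people give about 913 events and 99.9% power. The claim is consistent as a lower bound, and the present point does not depend on it.

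**2. How much of each window lies in the suspect period.** Suppose the suspect period before diagnosis is L years, taking L from the plan's own three shifts. Without a lag, the share of an n-year window that falls inside it is min(1, L/n).

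| Window n | L = 0.5 | L = 1 | L = 2 |
|---|---|---|---|
| 1 year | 50% | 100% | 100% |
| 5 years | 10% | 20% | 40% |

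A current HbA1c or current treatment is the limiting case of a very short window. This is why those measures and the 1-year windows are the most exposed.

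**3. Size for a yes/no current exposure, true hazard ratio 1.** Assumed inputs, neither given in the document: a share p of the risk set is exposed, and a fraction f of the otherwise unexposed cases start the drug because of occult cancer. Here f means starts that count as exposure and that adjustment for glucose does not remove. The apparent ratio compares exposure odds in cases with those in the risk set:

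[(p + (1 − p)f) / ((1 − p)(1 − f))] / [p / (1 − p)].

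For p = 0.10 and f = 0.05: (0.145 / 0.855) / (0.10 / 0.90) = 1.53.

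| p | f = 1% | f = 2% | f = 5% | f = 10% |
|---|---|---|---|---|
| 10% | 1.10 | 1.20 | 1.53 | 2.11 |
| 20% | 1.05 | 1.10 | 1.26 | 1.56 |
| 30% | 1.03 | 1.07 | 1.18 | 1.37 |
| 50% | 1.02 | 1.04 | 1.11 | 1.22 |

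**4. A second illustration, by time since starting the drug.** Assumed apparent hazard ratios are a in months 0–6, b in months 6–12 and 1.0 afterwards, with a constant background rate and mean exposed follow-up of T years. The pooled ratio is (0.5a + 0.5b + (T − 1)) / T.

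| a, b | T = 2 | T = 4 | T = 6 |
|---|---|---|---|
| 3.0, 1.5 | 1.63 | 1.31 | 1.21 |
| 2.0, 1.3 | 1.33 | 1.16 | 1.11 |

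Steps 3 and 4 describe a binary drug contrast only. They do not represent cumulative dose, and they do not cover Aim 2.

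**5. Cost of a primary lag.** Assume events are spread evenly over 10 years and the first L years are lost. Power for a hazard ratio of 1.4 is Φ(½√d × ln 1.4 − 1.960).

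| Events without lag | No lag | 6 months | 1 year | 2 years |
|---|---|---|---|---|
| 913 | 99.9% | 99.9% | 99.8% | 99.5% |
| 500 | 96.4% | 95.6% | 94.6% | 92.0% |
| 278 | 80% | 78% | 76% | 71% |

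For subsets of 500 or more events, the range the plan itself discusses, power is no obstacle to a primary lag.

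**The case against.** The strongest reply is that the plan already deals with reverse causation. It names the problem, looks for early peaks, shifts diagnoses by three lengths and lists lagged predictors, so a reader would see both lagged and unlagged results. The article also never says that the unlagged estimate outranks the shifted one. Its reference to a primary analysis concerns software and model class, and a journal article may leave the ranking to a fuller plan. Allowing for triggering HbA1c and glucose acts on the very path from cancer to glucose to treatment, and the 3-purchase rule excludes a drug bought only once or twice before diagnosis.

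Much of this stands. That the unlagged model is the main one is an inference, though a fair one: the model definitions carry no lag, and the paragraph after the date shift refers back to what was just outlined as sensitivity analysis. The safeguards reduce the problem for Aim 3 but need not remove it. They cannot help Aim 2, where HbA1c is itself the exposure.

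A reader might infer that the plan concedes its main estimates are contaminated. It does not: it speaks of a possibility and of changes that may occur. A reader might also take the illustrations as estimates of the bias, but their inputs are assumed. For cumulative dose even the direction is open, because recent starters have the lowest dose, so an early peak could flatten or reverse a dose trend. That a 1-year lag would remove all the excess is true in step 4 only because the excess was set to end at 12 months. Finally, 1.4 is the plan's power illustration, not a decision threshold.

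**Conclusion.** The point holds in a limited form. The Aim 2 and Aim 3 models are defined on exposure up to the risk date, the plan recognises a mechanism that may distort that exposure, and no lagged result is designated primary or given precedence if results differ. The main hazard ratios are exposed to reverse causation. The document does not show that they suffer from it.

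The size cannot be computed from the document. For a binary drug exposure, under the assumed p and f, it runs from negligible (1.02) to well above 1.4 (2.11). No figure is offered for HbA1c or cumulative dose. The weakness is worth correcting because the remedy is already among the planned analyses and costs little. The planned checks keep it from being a fatal flaw.

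**What to change.** In Statistical analyses, where the Aim 2 and Aim 3 models are defined, pre-specify one of the plan's own lags as the primary exposure definition. One year is a reasonable example. The article argues for none of the three lengths, and what matters is fixing one in advance.

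Suggested content: at any time t, HbA1c, glucose, treatment status and cumulative dose use only records up to t minus the lag, for cases and non-cases alike. The 1-to-5-year windows end at t minus the lag, and the current level is replaced by the level one lag earlier. The unlagged model and the other two lag lengths are reported as sensitivity analyses. State that conclusions rest on the lagged estimate, and that any difference from the unlagged one is reported and discussed as possible reverse causation or short latency.

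The change is wording and recoding. The cost is that some recent exposed person-time and events are counted under the earlier status. Power falls slightly (step 5; more noticeably in subsets near 278 events), and a genuine short-latency effect could be diluted. Reporting the unlagged model alongside keeps such an effect visible.
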